# 6.1 Randomization and Blinding*.* For each infant born to a mother that has provided consent, eligibility will be assessed. One consent document is sufficient for both the mother and her baby. Thus, there will be a two-part screening to first determine maternal eligibility, and then to determine infant eligibility. IRB approved staff will screen infants based on inclusion/exclusion criteria. The site coordinator, or research staff, will discuss eligibility with approved staff and if the patient is eligible, input patient data into the web based system. Once data is inputted, research staff will randomize eligible families 1:1 using web-based block randomization stratified by study site to receive EA or placebo. Multiples (i.e. siblings) will be randomized to the same treatment arm. Staff will not see the treatment arm that patients are assigned to. Rather, treatment arm and patient information will be sent to each site’s investigational pharmacy, where study drug will be drawn and sent to the patient’s room. The staff member who performed randomization will see a confirmation message that randomization was successfully sent to the pharmacy. The investigational pharmacy is unblind to patient’s allocation. Participants, treating clinicians, and study staff will all be blinded to allocation. Randomization must occur within the first 4 hours of life. Outcome assessors and statistical summaries for trial monitoring will be unaware of group allocation. Unblinded data evaluation during the trial will be restricted to a designated study statistician and the DSMB. We will unblind investigators and begin analyses only after all data collection forms are completed, data queries resolved, and data are locked for analysis.

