# Data Management and Confidentiality

# The hypothesis of the primary outcome is that the incidence of composite adverse events (NEC, LOS, or death) is significantly different in ELBW infants receiving EA and infants receiving placebo. Based on 1,000,000 simulations for the group-sequential test for comparing two proportions and O’Brien-Fleming alpha spending method for two interim analyses, we need 382 infants in each arm to reach 90% power to test the hypothesis of the primary outcome using a two-sided significance level of 0.05. We base our event rates for the standard of care (i.e. infants receiving EA) on published literature regarding risk of adverse events with each day of antibiotics, on recent data from the Vermont Oxford Network ^51^, and upon data from the Pediatrix CDW. We used 13.5% and 22% for the placebo and EA groups, respectively in the sample size calculations. The effect size (odds ratio 1.35 *per day of* EA) is based on the scant literature available to assess the risk-benefit ratio of EA. Another assumption made in the calculation includes intraclass correlation (ICC) of 0.01. Based on in-house data for babies born at Magee-Womens Hospital in the past 4 years, we estimate that 20 out of 100 infants will be twins or triplets. Anticipating a 5% attrition rate, we will recruit 802 infants (from ~670 families; 401 infants in each arm) to reach at least 90% power.

Given recent admission numbers and anticipated moderate growth at NANO study sites, we estimate that the 7 sites will admit 2700 infants ≤28 weeks GA over a 4-year period, allowing 6 months for trial rollout and 3-6 months in Year 5 for final analyses and preparation of manuscripts. We estimate that 1755 infants (65% of total) will meet eligibility criteria.  Based upon our surveys of recently delivered mothers (see above) and our experience with NICU RCTs^173,174,176^, we believe it is reasonable to expect that parents of 30-50% of these 1755 infants will elect to participate. A 46% consent rate will yield approximately 807 study subjects (29.9% of total admissions ≤28 weeks GA).  If the rate of missing outcome data is 5%, then the trial will have 766 subjects – yielding 383 patients per group. This randomized clinical trial will thus have excellent power to detect clinically meaningful differences between the EA and placebo groups with respect LOS/NEC/Death. If the consent rate is lower than 46%, we will add enrollments at 1-2 additional sites.

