We will compare the distribution of baseline variables between study arms to assess randomization success. To summarize continuous variables, we will use means and standard deviations or medians and interquartile range, and will use frequencies and percentages for categorical variables. Graphical methods (e.g., histogram, boxplot) will be used for assessing the overall shape of a continuous variable. No formal statistical hypothesis tests will be performed to avoid unnecessary testing.

The primary analysis is an intent-to-treat (ITT) analysis that includes two interim analyses at 1/3 and 2/3 enrollment, and a final analysis using O'Brien-Fleming stopping rules. The primary test for the primary outcome is that the **incidence of composite adverse events is significantly different in ELBW infants receiving EA compared to infants receiving placebo**.

The primary outcome will be analyzed using a generalized linear model (GLM) with a log link fitted via generalized estimating equations (GEE) with exchangeable working correlation matrix and employ robust variance estimates. This will account for non-independence of observations due to clustering of infants within families. The exchangeable correlation was selected primarily due to parsimony. Furthermore, infants within a twin or triplet can be considered exchangeable (i.e., the assigned infant ID within a set is arbitrary). The model will include treatment as fixed effects adjusted for site and gestational age. The primary hypothesis will be tested via the Wald test of the treatment assignment and effect estimates will be presented using risk ratios (RR) with 95% confidence intervals (CI).

In secondary analyses, we will examine each component (NEC, LOS, death) of the composite adverse outcome separately using the same analytic approach as the primary outcome.

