*Microbiome analysis*. For microbiome analyses in **Aims 2 and 3**, assuming that the alpha diversity is normally distributed, we need a total samples size of 78 over two groups (39 per group) to detect a 43% reduction in alpha diversity (from 1.75 to 1) at the 14 day timepoint with a 5% level of significance and 90% power. This effect size is based upon our preliminary data and also published reports, as described in the Research Strategy. We will easily exceed power to discern differences in alpha diversity but will plan for much larger sample size to allow not only for taxonomic analyses across samples from EA and placebo groups, and also subgroups (as defined above for Aim 1 analysis).

Bacterial 16S rRNA gene sequences will be extracted from infant samples, amplified, and sequenced on the Illumina Miseq according to established protocols used routinely by the [name], [name], and [name] laboratories. In analyses of these samples, we shall investigate three important parameters, namely, the alpha diversity (Richness and Shannon Index), the beta diversity, and the differential abundance of individual bacterial taxa. We hypothesize that samples from EA subjects will contain increased abundance of pathogens (e.g. *Enterococcaceae* and *Enterobacteriaceae)* and decreased abundance of commensal anaerobes (e.g. *Bacteroidaceae* and *Bifidobacteriaceae*) relative to samples from infants receiving placebo.

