**For Aim 2**, bacterial 16S rRNA gene sequences from weekly fecal samples collected during the first month of life from each experimental group will be compared at each time point and also with longitudinal trend analyses. Temporal trend analysis of alpha diversity will be performed with the Constrained Linear Mixed Effects (CLME) models package developed by the [name] group. The analysis does not make any distributional assumptions, and takes into account the repeated measurement feature in the data since longitudinal measurements are obtained on each subject. The method is also robust against heteroscedasticity as it is based on Best Linear Unbiased Predictor (BLUP) residual bootstraps. The temporal trend analysis of beta diversity will be performed using an extension of PERMANOVA for repeated measurements data. As for temporal differential abundance analyses within each experimental group, we will use the newer version of ANCOM for detecting trends in abundance, while allowing repeated measurements as well as covariates. ANCOM was developed by [name] and colleagues, and is based on the software ORIOGEN developed by [name]. Note that differential abundance analyses of taxa between groups cannot be performed using standard ANOVA or t-test because these data reside inside a simplex. Currently, among the many methods used in the literature for differential abundance analyses, ANCOM is the only method that controls the false discovery rate at the desired nominal level.

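### Aim 2 microbiome analyses name no family-level correlation although siblings are randomized together, and the longitudinal taxa analysis is specified only within arms

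*Protocol*

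**What the plan says.** **Randomization.** Protocol Section 6.1 randomizes families 1:1 within site: "Multiples (i.e. siblings) will be randomized to the same treatment arm".

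**Primary outcome.** Section 16.0 fits a GEE model with an exchangeable working correlation and robust variance, and gives the reason: "This will account for non-independence of observations due to clustering of infants within families". The components (NEC, LOS, death) use the same approach. The sample size text adds "Another assumption made in the calculation includes intraclass correlation (ICC) of 0.01".

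**Aim 2.** Section 2.0 states a between-arm hypothesis: EA samples should show lower diversity, more pathogens and fewer commensal anaerobes than placebo samples. The Aim 2 paragraph of Section 16.0 opens by planning a comparison of the groups at each time point and by longitudinal trend. It then names three methods:
- CLME for alpha diversity, which "takes into account the repeated measurement feature in the data since longitudinal measurements are obtained on each subject".
- An extension of PERMANOVA to repeated measurements for beta diversity.
- For taxa over time: "As for temporal differential abundance analyses within each experimental group, we will use the newer version of ANCOM". This version is said to allow repeated measurements and covariates.

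Family is not mentioned in any of the three. The Aim 2 sample size, "we need a total samples size of 78 over two groups (39 per group", states no ICC.

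**The concern.** There are two separate matters.

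**Sibling correlation.** Siblings share a mother and, by design, an arm. The protocol itself lists mode of delivery, gestational age, diet and maternal antibiotic exposure as influences on the infant gut microbiota. Siblings share at least gestational age and maternal antibiotics, so positive correlation between them is to be expected. When whole families are allocated to one arm, an analysis that recognises only the infant understates the variance of the arm contrast. The protocol also relies on ANCOM holding the false discovery rate at its nominal level, and unmodelled sibling correlation would weaken that assurance.

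**Within-arm trends for taxa.** A trend that is significant in one arm and not in the other is not evidence that the arms differ. If the only longitudinal taxa analysis is run arm by arm, the longitudinal part of the pathogen and anaerobe hypothesis has no test that compares EA with placebo.

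**Working it through.** **1. The plan's own Aim 2 figure.** The difference in alpha diversity is 1.75 − 1 = 0.75, with 39 per group, 5% significance and 90% power. No SD is given, so 78 cannot be reproduced directly. Taking the test as two-sided and solving for the SD by the normal approximation:

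SD = 0.75 × √(39/2) / (1.960 + 1.282) ≈ 1.02.

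The t-test version gives about 1.01, and an SD of 1.0 gives exactly 39 per group by the t-test. The figure is plausible and treats infants as independent.

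**2. Cluster sizes.** The protocol gives two descriptions, and they do not quite agree: "we will recruit 802 infants (from ~670 families; 401 infants in each arm") and "we estimate that 20 out of 100 infants will be twins or triplets". Taking all multiples as twins:
- *From the family count:* 802 − 670 = 132 pairs and 802 − 264 = 538 singletons. Σm²/Σm − 1 = (538 + 4 × 132)/802 − 1 = 0.329.
- *From 20% of infants:* 80 pairs (722 families) and 642 singletons. Σm²/Σm − 1 = (642 + 4 × 80)/802 − 1 = 0.20.
- *From 20% of families being twins* (670 × 1.2 = 804, close to 802): (0.8 + 0.2 × 4)/1.2 − 1 = 0.333. This is almost the same as the first and sets the upper end of the range.

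**3. Design effect and true type I error.** DE = 1 + (Σm²/Σm − 1) × ICC. A test that ignores family has true two-sided error 2 × [1 − Φ(1.96/√DE)]. The only ICC in the protocol is 0.01, for the primary binary outcome. The other values are assumptions.

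| Sibling ICC | 80 pairs: DE | 80 pairs: true error | 132 pairs: DE | 132 pairs: true error |
|---|---|---|---|---|
| 0.01 | 1.002 | 5.02% | 1.003 | 5.04% |
| 0.1 | 1.020 | 5.2% | 1.033 | 5.4% |
| 0.3 | 1.060 | 5.7% | 1.099 | 6.2% |
| 0.5 | 1.100 | 6.2% | 1.165 | 6.9% |
| 0.7 | 1.140 | 6.6% | 1.230 | 7.7% |
| 1.0 | 1.200 | 7.4% | 1.329 | 8.9% |

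With the factor 0.333, the error at ICC 0.7 is 7.8%.

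**4. Simulation check.** A t-test with whole families randomized, 10,000 runs per setting, at ICC 0.3, 0.5 and 0.7 gave 5.5%, 5.8% and 6.6% with 80 pairs, and 6.1%, 7.1% and 7.6% with 132 pairs. These agree with the formula.

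**5. Power.** Even at ICC 1.0 with 132 pairs, 78 infants become 78 × 1.329, rounded up to 104. The effective size of 802 infants is 802/1.329 ≈ 603.

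**6. Taxa over time: the texts side by side.**
- Aim 2 asks about EA against placebo.
- The opening of the Aim 2 paragraph promises a longitudinal comparison in general terms.
- The one longitudinal method named for taxa is confined to each arm.
- Aim 3 shows the missing step. It models growth curves in each group, then compares the groups, and it adds a taxon-by-group interaction in the regression. Nothing equivalent follows the ANCOM sentence.

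**The case against.** The strongest reply is that the sibling point is drawn from silence. The CLME sentence explains why the method suits repeated data; it is not a full list of random effects. No permutation scheme is stated for PERMANOVA, and ANCOM is said to accept covariates. Nothing in the protocol says that siblings are taken as independent, it plainly recognises family clustering elsewhere, and an analysis plan not shown here could add the family level. This stands as far as it goes. A reader might infer that the microbiome p-values *are* too small, or that infants *will* be permuted freely. The documents support neither; the point holds only if family is left out. It is still worth making, because the protocol does address correlation for these models and stops at the infant, whereas for the primary outcome it goes up to the family.

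A reader might also infer that Aim 2 has no longitudinal between-arm test at all. That goes too far. The Aim 2 paragraph plans between-arm comparison at each time point and by trend, and the within-arm wording attaches only to temporal differential abundance. Aim 2 can also be read as a hypothesis about levels, which weekly between-arm comparisons address. Nor does the text say that conclusions will be drawn by setting significance in one arm against its absence in the other. What remains is that the paragraph promises longitudinal comparison and names no between-arm method for it in taxa.

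Aim 3 should not be drawn into the taxa point. It uses CLME and LASSO-type regression, compares the groups explicitly, and is exploratory.

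Finally, the error formula is for a two-arm test on one value per infant. It was not derived for bootstrap trend tests, PERMANOVA or ANCOM, so it indicates size only.

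**Conclusion.** The point holds in two limited parts.

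- **Family level.** The Aim 2 methods name only within-infant correlation. Followed literally, they would give mildly anti-conservative between-arm tests. The inflation is modest in the assumed range and negligible at the protocol's only stated ICC. Its size depends on a sibling microbiome ICC that the documents do not give, on all multiples being twins, and on infants with stool samples having the same mix of multiples as the whole trial.
- **Longitudinal taxa.** No between-arm longitudinal test is named for taxa abundance. This follows from the text and needs no numerical assumption.

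The primary outcome and its components already model family and are unaffected. Both parts should be corrected before the microbiome data are analysed; neither threatens the trial's main conclusion.

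**What to change.** 1. **CLME and ANCOM mixed models:** add a family level above the infant.
2. **PERMANOVA:** state the permutation scheme, permuting arm labels by whole family within site, to match how arms were allocated.
3. **Longitudinal taxa:** fit one model over both arms and test the arm and arm-by-time terms. Within-arm trends can be kept as description.

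The cost is a few sentences of specification, minor programming and slightly wider intervals. No extra infants are needed, since enrolment of about 802 far exceeds the 78 stated for alpha diversity under any sibling correlation.

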# They will monitor all aspects of study performance (e.g., enrollment, data processing time) and protocol compliance (e.g., randomization), as well as adherence to established adverse event reporting and event adjudication procedures. They will regularly provide reports to the clinical site coordinators addressing scheduling and delinquency. The project manager and PIs will conduct data monitoring site visits per a predetermined plan, prioritizing sites where specific data issues are identified or data concerns arise (risk-based monitoring).

16.2 Online Portal. The center of the NANO trial’s communications system will be a portal accessible via a password-protected study website which will be maintained by the DCC. The site will be used for day-to-day communications among the NANO study team by providing immediate communication, effective collaboration and project management. Access will be restricted to study investigators, research staff and committee members via unique usernames and passwords. The DCC’s password policy is consistent with National Institute of Standards and Technology (NIST) password policy. The primary interface is a collection of organized and individual web features, each representing a single tool which will vary in presentation and availability based on a defined user’s role (e.g., investigator, clinical site coordinator) and group association(s) (e.g., clinical site, committee membership).

16.3 Missing data. Despite best efforts to obtain follow-up data, we anticipate some loss-to-follow-up. We will describe the extent and reasons that data are missing, summarizing the proportion of patients with missing data for each outcome and by study arm and by site. We will compare baseline patient characteristics between those who have complete outcome data and those that do not. It is anticipated that, on rare occasion (<<5% of subjects), even before culture results are received, an attending neonatologist caring for a study subject will elect to prolong antibiotic therapy beyond 72 hours (e.g. due to clinical deterioration). This will be classified as a protocol deviation. Such infants will be analyzed according to intention to treat principles.

Optimal ITT includes analysis of data from all subjects randomized and cannot be directly adopted in the presence of missing data. To resolve this, we chose multiple imputations to conduct the ITT analyses. Multiple imputed datasets will be generated using multivariate imputation by chained equations, an approach designed for multivariate data that can accommodate mixed data types. We will use predictive mean matching and logistic regression to impute continuous and binary outcomes, respectively. We will generate 100 imputed datasets to maintain power, although 3-5 imputed datasets are usually sufficient to obtain excellent results^196^. We assume that missing outcome data are missing-at-random (MAR) in that they can be imputed reasonably well from the observed study data. We will perform imputation based on the study arm to which the patient was assigned. Auxiliary variables for the imputation model will include patient baseline variables (e.g., age, sex, race, and study site).

16. 4 Sensitivity analyses. We will assess the robustness of study findings to assumptions about missing data, the primary analysis population, and covariates used for adjustment. Specifically, we will perform the following:

- We will conduct a missing-not-at-random (MNAR) sensitivity analysis using control-based imputation in which all data are imputed based on the placebo arm.
- Since ITT generally biases towards no difference, we will perform a per-protocol analysis in which the complier average causal effect (CACE) will be estimated by using the treatment assignment as an instrumental variable.
- Baseline variables that were found to be strongly imbalanced between the treatment groups will be added as adjustment variables to the primary analysis model.

16.5 Data storage and security. Initial stages of data management will be done by experienced clinical data managers, database developers, data research associates, and data processing staff, supported by computer system analysts, programmers, and information technology specialists. These persons will be responsible for data quality and timeliness, documentation of processes and procedures, and training of data management staff.

Data will be entered directly into a secure, backed-up, 24-hour, web-based database using electronic forms developed by the BDMC staff with the assistance of project investigators and statisticians. Data entry screens will incorporate range and logical edit checks, both within and across forms. A data monitoring plan written before the start of data collection, will serve as a reference guide for the development of case report forms, data handling conventions, reporting, data dictionaries, supporting meta data, as well as project closeout activities, communication and coordination plans among the PIs, clinical teams, sites coordinators, and staff and faculty-level statisticians.

Identifiable medical record information will be used and will remain at each site until the study is completed in 2025. PHI information will not be shared across sites.

The link between your PHI and the study ID code will be destroyed ten years after study completion. Records of your baby will be maintained until he/she is 23 years of age. After that time, identifiers will be destroyed, and research data will be coded and retained anonymously indefinitely.

# Provisions to Monitor the Data to Ensure the Safety of Subjects

17.1 Safety monitoring and event reporting. As with any experimental procedure, there may be adverse events or side effects that are currently unknown and certain of these unknown risks could be permanent, severe or life threatening. We will capture the major potential adverse events related to EA during the study and examine each adverse event using standard reporting methodology. Research staff will strictly comply with IRB policies for the reporting of adverse events. To assist with reporting of adverse events, an event table will be distributed to all sites prior to enrollment.

*Definition of an adverse event (AE).* Any untoward medical occurrence in a subject temporally associated with the trial protocol, whether or not it is considered causally related to the trial protocol. Examples include: (1) significant or unexpected worsening or exacerbation of the condition under study, (2) or new conditions detected or diagnosed after protocol initiation even though it may have been present prior to the start of the study.

*Definition of a serious adverse event (SAE).* Any untoward medical occurrence during the index hospitalization that: (1) results in death, (2) is life-threatening, or (3) results in disability/incapacity.

All AEs and SAEs will be recorded from the time of randomization until hospital discharge. AEs and SAEs will be solicited from parents of subjects, attending physicians, and bedside nurses; the medical record will also be reviewed daily for the presence of events. Notification of coordinating center regarding any SAE will take place within 48 hours of recognition. The coordinating center will then be responsible for notifying the DSMB regarding all SAEs within 48 hours. When an AE/SAE occurs, it will be the site PI’s responsibility to review the pertinent records, notes, laboratory, and radiographic data. This information will be recorded along with the site PI’s impression of the diagnosis. The site PI will assess causality between the event and the study protocol using best clinical judgment, and this will be reviewed by the DSMB who will recommend if follow-up or modification of the study protocol is necessary. All deaths will be reviewed by the DSMB within 30 days of reporting said event.

17.2 Data safety and monitoring board (DSMB). The University of Pittsburgh Office of Clinical Research, Health Sciences / CTSI will provide the logistical management and support of the DSMB. A letter of support can be provided to sites, if needed. We propose to include neonatologists, maternal fetal medicine specialists, infectious disease specialists, and a statistician and/or epidemiologist experienced in the conduct of clinical research and unaffiliated with any study team members. Members will consist of persons independent of the investigators who have no financial, scientific, or other conflict of interest with the study. Written documentation attesting to absence of conflict of interest will be required. The DSMB will review the study protocol prior to study rollout and will meet on a semi-annual basis to review recruitment, retention, data completeness, protocol deviations, and adverse events. Safety data will be examined on an ad hoc basis if safety concerns arise from trial data or from external research or literature.

The DSMB will:

1. Review the research protocol, informed consent documents and plans for data and safety monitoring;
2. Evaluate the progress of the study, including periodic assessments of data quality and timeliness, participant recruitment, accrual and retention, participant risk versus benefit, adverse events, unanticipated problems, performance of the trial sites, and other factors that can affect study outcome;
3. Consider factors external to the study when relevant information becomes available, such as scientific or therapeutic developments that may have an impact on the safety of the participants or the ethics of the study;
4. Review clinical center performance, make recommendations and assist in the resolution of problems reported by the PI;
5. Protect the safety of the study participants;
6. Report on the safety and progress of the study;
7. Make recommendations to the PI, and if required, to the NIH / NICHD concerning continuation, termination or other modifications of the study based on the observed beneficial or adverse effects of the treatment under study;
8. Monitor the confidentiality of the study data and the results of monitoring;
9. Assist the PI by commenting on any problems with study conduct, enrollment, sample size and/or data collection.

The first meeting will take place before study initiation to discuss the protocol, approve the commencement of the study, and to establish guidelines to monitor the study. A safety officer (Chairperson) will be identified at the first meeting. This person will be the contact person for serious adverse event reporting. The DSMB will review the final protocol before commencing enrollment and then meet semi-annually and at any other needed interval (based on reports) to ensure that no serious adverse consequences occur because of either administering or withholding the intervention. An emergency meeting of the DSMB will be called at any time by the Chairperson should questions of patient safety arise.

DSMB reviews will consider the occurrence of adverse events, problems with loss of confidentiality, or other unanticipated problems, and will consider whether the anticipated benefit-to-risk ratio of study participation is altered by the findings in the safety monitoring process. Particular attention will be given to confirm that the study protocol is protecting the privacy of research subjects as anticipated. The following will be reported to the IRB: date of data and safety monitoring; summary of adverse event data including an assessment of intervention causality; summary of the assessment of relevant scientific literature and its impact on the design of the study; summary of procedural reviews conducted to ensure subject privacy. This report will be accompanied by a final conclusion regarding changes of the anticipated benefit-to-risk ratio and recommendations related to continuing, changing, or terminating the study. Recommendations to change the study will be accompanied with a detailed rationale for the proposed changes.

17.3 Interim analyses and stopping rules. The NANO Coordinating Center will conduct two interim analyses and a final analysis using O’Brien and Fleming stopping rules defined *a priori* controlling for an overall Type I error rate of 0.05. The first and second interim analyses will be scheduled at approximately 1/3 and 2/3 enrollment, respectively. The DSMB will review recruitment, safety, data collection, and analysis results at each interim analysis. Before trial completion, only the DSMB and a designated study statistician will have access to unblinded data. **During the interim assessments, the DSMB could recommend early trial termination due to unanticipated safety concerns, or due to one or more of the following reasons:**

1. A significant difference is found for the study hypothesis and a Z test statistic significance bound is crossed because of excess incidence of a composite adverse outcome (NEC, LOS, or death) in the EA arm.
2. A significant difference is found for the study hypothesis and a Z test statistic significance bound is crossed because of excess incidence of a composite adverse outcome (NEC, LOS, or death) in the placebo arm.
3. Failure to obtain success in the implementation of the trial either through failure to accrue subjects at the necessary rate, improper data handling, or inability to implement study protocols.

